Although a FOBT is relatively simple, inexpensive, and noninvasive compared to colonoscopy, the rate of FOBT screening varies from 20% to 71% among countries[9]. In Korea in 2012, the rate of FOBT screening was only 25.7%[12]. Several barriers, including health system, provider, and patient factors, contribute to the low rate of FOBT screening[13–16]. In Korea, the system-related barriers to an efficient screening process have been reported to be the requirement for two consecutive clinic visits to receive the stool device and submit the sample, and the use of a stool container that has a short, thick sampling probe to collect stool samples[17]. To overcome these barriers, two interventions are being considered. The first is to distribute stool-collection devices by mail, which requires only one clinic visit to submit the sample. The second is to provide a stool sampling kit consisting of a small test tube including a longer, thinner sampling probe that is easier to poke into the stool to collect stool specimens. Through these interventions, this study will determine the most effective strategy to increase compliance and satisfaction in FOBT screening. This determination is based on the assumption that changing the stool-collection process (especially as regards the type of stool-collection device) will not affect the results of FOBTs, but may affect compliance and satisfaction. We will therefore compare the rates of positive FOBT results between the two stool devices to validate our assumptions.

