### Interventions

There will be four groups: sampling kit received by mail, conventional container received by mail, sampling kit received at the clinic, and conventional container received at the clinic (control group). Sampling kits are being purchased from Eiken Chemical Co., Ltd., Tokyo, Japan. Compared to the currently used conventional container, the new sampling kit is thinner and smaller, with a thin (4.2 cm long) sampling probe attached to the cap that allows easier insertion into the stool. The tip of the sampling probe has a spiral groove to collect stool specimens (Figure 2). The sampling probe with the collected stool (approximately 10 mg) may then be reinserted into the kit. These stool specimens are analyzed in an OC-SENSOR DIANA machine (Eiken Chemical Co., Ltd., Tokyo, Japan) designed for quantitative immunochemical FOBTs and the sampling kits fit this equipment. Stool specimens in conventional containers are transferred to sampling kits for immunochemical FOBTs at the laboratory because the conventional containers do not fit the analyzer. Mailed sampling kits or conventional containers will include an instruction leaflet. All participants who receive stool devices will be instructed in methods of stool collection via telephone or face-to-face by research staff.

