**Illustrations of stool devices: (a) conventional container; (b) sampling kit.**

### Outcome measures

The primary outcome will be compliance with FOBT screening; compliance will be defined as the proportion of individual participants who submit stool specimens to the National Cancer Center within two weeks following receipt of collection devices. The secondary outcome will be participant satisfaction and intention to be rescreened in the next screening round as assessed by questionnaire at the clinic. The questionnaire will use a five-point Likert scale (1 = strongly disagree, 2 = disagree, 3 = uncertain, 4 = agree, 5 = strongly agree) with three dimensions: satisfaction with each process, from receiving stool devices to submission of specimens at the clinic; overall satisfaction with the entire process; and intention to be rescreened. The tertiary outcome will be the rates of positive FOBT results using sampling kits vs. conventional containers. Positive results are defined as those exceeding 100 ng/mL blood. All participants who undergo FOBT will be informed of the screening results via mail within three weeks, and those whose results are positive will be recommended to undergo colonoscopy. Colonoscopy or further biopsy for abnormal lesions will be performed by highly qualified colonoscopists upon provision of written consent at the NCC. Histopathological results will allow comparison of the detection rates of advanced adenoma or cancer between sampling kits and conventional containers. All outcomes of the study will be explained to respondents upon interview and prior to obtaining written informed consent.

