### Sample size calculation

Study participants will be divided into two groups according to the method of receiving the stool-collection device. To determine the sample sizes of two groups, we will establish the null hypothesis (H_0_) and alternative hypothesis (H_1_) using the difference *p*_*1*_*-p*_*2*_, where *p*_*1*_ is the expected compliance rate in the group receiving collection devices by mail and *p*_*2*_ is the expected compliance rate in those receiving them at a clinic.$$\begin{array}{l} H_{0}:p_{1}=\;p_{2}\left(\delta =p_{1}-\;p_{2}=0\right)\;\text{vs}.\\ H_{1}:p_{1}>p_{2}\left(\delta =p_{1}-\;p_{2}>0\right) \end{array}$$

The expected compliance rate of participants visiting a clinic is based on that observed in 2010 by the NCSP, which was 30.8%, and the compliance rate of participants receiving stool devices by mail is estimated at 36% based on the assumption that the rate will be at least 5% greater.$$N=\frac{{\left\{Z_{\frac{\alpha }{2}}\sqrt{\left(r+1\right)\bar{p}\left(1-\bar{p}\right)}+Z_{\beta }\sqrt{rp_{1}\left(1-p_{1}\right)+p_{2}\left(1-p_{2}\right)}\right\}}^{2}}{r{\left(p_{1}-p_{2}\right)}^{2}}$$

Based on the above formula, 1,398 people will be needed in each group to detect the difference *p*_*1*_*-p*_*2*_ in the proportions using a two-tailed test and 80% power (1-β) at a 5% significance level. However, continuity correction tests will be needed to estimate very closely approximate values, and thereby a sample size of 1,438 in each group will be required. Finally, to allow for a 20% loss to follow-up, we will enroll an additional 350 participants per group, resulting in a final total for each group of 1,798 participants; thus, a total of 3,596 participants will be enrolled in the study.

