### Statistical analysis

Compliance rates for FOBT screening will be compared among the four groups by a chi-square test. The satisfaction and intent to rescreen using a FOBT will be assessed by analysis of variance (ANOVA). The rates of positive FOBTs and the rates of advanced adenoma or cancer detected by colonoscopy using the different stool devices will also be analyzed by a chi-square test. The adjusted odds ratios (ORs) and 95% confidence intervals (CIs) of each outcome will be calculated using multiple logistic regression. All data will be analyzed using the SAS software, version 9.2 (SAS Institute, Inc., Cary, NC, USA).

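### The check that the device leaves FOBT results unchanged uses only positive/negative at 100 ng/mL; a supporting comparison of analyser concentrations would be a cheap improvement

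*Protocol article*

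**What the plan says.** The Background rests the comparison of devices on the assumption that changing the collection process "will not affect the results of FOBTs, but may affect compliance and satisfaction". It then names the check: "We will therefore compare the rates of positive FOBT results between the two stool devices to validate our assumptions".

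Outcome measures fixes the form of that check. "The tertiary outcome will be the rates of positive FOBT results using sampling kits vs. conventional containers", and "Positive results are defined as those exceeding 100 ng/mL blood". Statistical analysis assigns a chi-square test to "The rates of positive FOBTs and the rates of advanced adenoma or cancer detected by colonoscopy using the different stool devices". No comparison of measured concentrations is named.

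Interventions describes the laboratory side. The analyser is "designed for quantitative immunochemical FOBTs and the sampling kits fit this equipment". Kit specimens are loaded by the participant on the probe (about 10 mg). Those from the other device take an extra step: "Stool specimens in conventional containers are transferred to sampling kits for immunochemical FOBTs at the laboratory".

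**The concern.** The two devices differ in who loads the kit tube and when. If that difference matters, it could act on the measured concentration across the whole range of readings. A positive/negative outcome sees such a shift only through the specimens that cross 100 ng/mL, and with a low positive rate few do.

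The Background gives the comparison a validating role. A non-significant chi-square with low power could then be taken as confirmation that readings do not depend on the device, and the devices would be compared on compliance with that question still open. A more sensitive measure of a general shift appears to be available, since a numerical cut-off on a quantitative analyser implies a numerical reading.

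**Working it through.** **What the article supplies.** It gives no power, sample size or expected positive rate for the device check, so there is no stated figure to reproduce for this point. The only sample size concerns the distribution method: 1,438 / 0.8 = 1,798 per group, 3,596 in total. With 1:1:1:1 allocation the device factor also has about 1,798 per arm.

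**Submitters per device.** Clinic compliance is taken as 30.8% ("based on that observed in 2010 by the NCSP, which was 30.8"%) and mail compliance as 36%:

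1,798 × 0.36 + 1,798 × 0.308 = 647 + 554 = 1,201; half of that is about 600 per device.

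Using a 5-point difference (35.8%) instead gives 1,798 × (0.358 + 0.308) / 2 = 599, so the figure is stable.

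**Information kept by the cut.** Assume normal log-concentration and a small shift. A cut with positive fraction p, at standard normal point c, keeps φ(c)² / [p(1 − p)] of the information. At p = 5%, c = 1.645 and φ(c) = 0.103, so the share is 0.0106 / 0.0475 = 22%. At 3%, 7% and 10% positive it is 16%, 28% and 34%.

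Undetectable readings carry less information, so the cut then gives up less. At 5% positive it keeps 27%, 34%, 42% and 62% with 50%, 70%, 80% and 90% undetectable. At 10% positive with 80% undetectable it keeps 64%.

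**Power for a proportional loss.** Assumptions, none of them in the article: 600 per device, log-normal readings, 5% positive with the kit, readings below 10 ng/mL treated as tied, and container readings multiplied by 0.7 or 0.5. Positive rates after a 30% loss follow from the model. For 15% above 10 ng/mL, for example, the log SD is ln(10) / (1.645 − 1.036) = 3.78, the shift is ln(0.7) / 3.78 = −0.094 SD, and positivity falls from 5.0% to 4.1%. Simulated power, as the range over repeated runs:

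| Share above 10 ng/mL | Positive after 30% loss | Chi-square, 30% loss | Rank test, 30% loss | Chi-square, 50% loss | Rank test, 50% loss |
|---|---|---|---|---|---|
| 15% | 4.1% | 12-13% | 18-19% | 28-31% | 52-53% |
| 25% | 3.6% | 21-22% | 48-52% | 57-60% | 95-96% |
| 40% | 3.1% | 34-37% | 87-88% | 83-85% | 100% |

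With no device effect both tests reject about 5% of the time.

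**Where the gain disappears.** With only 10% above 10 ng/mL and 5% positive, power at a 30% loss is 7-8% (chi-square) against 8-10% (rank test). With 10% positive and 15% above 10 ng/mL, both are about 6-7%.

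**Other shapes of effect.** Same assumptions, with 15%, 25% or 40% above 10 ng/mL:
- Readings below the cut-off are halved and all positives are unchanged. Positivity is identical, yet the rank test rejects in about 50%, 95% and 100% of runs.
- Half of the positives drop to 60 ng/mL. Positivity is halved; chi-square power is about 62-64%, and rank-test power is only 4-7%.

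**The case against.** The strongest reply is that the planned endpoint fits its purpose. Positivity is the result that leads to a colonoscopy recommendation, and the article adds a second device comparison, detection of advanced adenoma or cancer. Nothing is contradicted, and a supplementary analysis might be found in a full protocol or SAP that is not shown. It is right that positivity is the programme-relevant measure. But the article itself fixes the outcome, threshold, test and validating purpose, so this is a comment on a stated choice and not on missing detail. The detection comparison is also binary and comes after a positive result, so it does not show a general shift in readings.

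A reader might go further and infer that most of the information is thrown away. The article does not support that: the loss depends on the positive rate and the share of undetectable readings, and in some plausible settings it is under half (38% lost at 5% positive with 90% undetectable).

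A reader might also infer that concentration should replace positivity as the main basis of the check. That fails on the last two scenarios above: a rank test can signal a difference when positivity is unchanged and can miss a halving of positivity near the cut-off. Nor does a rank test without a margin establish sameness any more than the chi-square does, which is why an interval for the shift matters more than the p-value.

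Finally, the article does not say that concentrations are recorded. That is an inference from the quantitative analyser and the numerical cut-off.

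**Conclusion.** The point holds as a low-cost improvement to a tertiary comparison. The check discards some information about a general shift in readings, by an amount that the article does not allow one to compute. For a uniform 30% loss, under the assumptions stated, chi-square power is about 12-37% against about 18-88% for a rank test, with little or no gain when few readings are detectable. A chi-square in that range cannot by itself confirm that the device leaves results unchanged. Positivity remains the right main check. The primary outcome, the sample size and the compliance conclusion are untouched.

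**What to change.** 1. In Outcome measures, keep the positive rate at the stated cut-off as the main device check, and add the analyser's concentration as a supporting tertiary outcome.
2. In Statistical analysis, compare concentrations between sampling kit and conventional container among submitters with a rank-based method (undetectable values as ties) or a censored-data method. Report the estimated shift or ratio with a 95% CI.
3. State that a non-significant chi-square on positivity will not alone be taken as validating the Background assumption.
4. Confirm that the concentrations are retained for every specimen.

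The cost is about two sentences and one more tertiary analysis, with no added participant, visit or assay provided the readings are kept. Like positivity, the comparison is made among submitters only, and it can flag shifts that leave positivity unchanged, so the two results should be read together. The cut-off and the colonoscopy recommendation stay as they are.

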### Sample size calculation

Study participants will be divided into two groups according to the method of receiving the stool-collection device. To determine the sample sizes of two groups, we will establish the null hypothesis (H_0_) and alternative hypothesis (H_1_) using the difference *p*_*1*_*-p*_*2*_, where *p*_*1*_ is the expected compliance rate in the group receiving collection devices by mail and *p*_*2*_ is the expected compliance rate in those receiving them at a clinic.$$\begin{array}{l} H_{0}:p_{1}=\;p_{2}\left(\delta =p_{1}-\;p_{2}=0\right)\;\text{vs}.\\ H_{1}:p_{1}>p_{2}\left(\delta =p_{1}-\;p_{2}>0\right) \end{array}$$

The expected compliance rate of participants visiting a clinic is based on that observed in 2010 by the NCSP, which was 30.8%, and the compliance rate of participants receiving stool devices by mail is estimated at 36% based on the assumption that the rate will be at least 5% greater.$$N=\frac{{\left\{Z_{\frac{\alpha }{2}}\sqrt{\left(r+1\right)\bar{p}\left(1-\bar{p}\right)}+Z_{\beta }\sqrt{rp_{1}\left(1-p_{1}\right)+p_{2}\left(1-p_{2}\right)}\right\}}^{2}}{r{\left(p_{1}-p_{2}\right)}^{2}}$$

Based on the above formula, 1,398 people will be needed in each group to detect the difference *p*_*1*_*-p*_*2*_ in the proportions using a two-tailed test and 80% power (1-β) at a 5% significance level. However, continuity correction tests will be needed to estimate very closely approximate values, and thereby a sample size of 1,438 in each group will be required. Finally, to allow for a 20% loss to follow-up, we will enroll an additional 350 participants per group, resulting in a final total for each group of 1,798 participants; thus, a total of 3,596 participants will be enrolled in the study.

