## Methods

### Trial design

The study will be conducted using a 2 × 2 factorial randomized control trial (RCT) design resulting in four groups. The first factor is the two methods of distributing stool devices (mailing vs. visiting a clinic), and the other is the two stool devices (sampling kit vs. conventional container). Thus, the study will be composed of four groups from two factors (allocation ratio1:1:1:1): (1) sampling kit received by mail; (2) conventional container received by mail; (3) sampling kit received at the clinic; (4) conventional container received at the clinic (control group) (Figure 1).

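### The trial is sized on mailing averaged over both devices without stating additivity, and the only compliance test named, a four-group chi-square, cannot identify the best strategy

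*Protocol article*

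**What the plan says.** Three statements in the protocol article have to be read together.

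- **Trial design.** "The study will be conducted using a 2 × 2 factorial randomized control trial (RCT) design resulting in four groups", with "allocation ratio1:1:1:1" allocation. The factors are route (mail or clinic) and device (kit or conventional container).
- **Sample size calculation.** "Study participants will be divided into two groups according to the method of receiving the stool-collection device". One rate is given per route. The clinic rate is "based on that observed in 2010 by the NCSP, which was 30.8" per cent, and "the compliance rate of participants receiving stool devices by mail is estimated at 36" per cent. No device effect is given, and nothing is said about whether the effects of route and device add.
- **Statistical analysis.** "Compliance rates for FOBT screening will be compared among the four groups by a chi-square test". Adjusted odds ratios from a multiple logistic regression are also promised, without a list of model terms.

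The Background sets the aim: "this study will determine the most effective strategy to increase compliance and satisfaction in FOBT screening".

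**The concern.** The mail-versus-clinic contrast is an average over the two devices. It describes mailing with each device only if mailing gives the same gain with both. The article neither states this nor names an estimate that would check it.

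Sub-additivity is possible. The Discussion expects both changes to make screening easier, so the second may add less once the first is in place. Participants "will be instructed in methods of stool collection via telephone or face-to-face by research staff", so a mailed kit might be explained by a different channel from one handed over at the clinic. These are reasons to look, not evidence of an interaction.

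The second gap is between test and aim. A policy maker must choose one of four combinations. A significant four-group chi-square says that the four rates are not all equal. It does not give the size of the mailing effect, the device effect or their interaction, and it does not say which combination is best.

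**Working it through.** **Inputs from the article.** 36% by mail, 30.8% at the clinic, two-sided 5%, 80% power, 1,438 per side before loss and 1,798 after. Equal allocation gives 1,438/2 = 719 or 1,798/2 = 899 per cell.

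**Inputs assumed.** The article gives no kit effect and no interaction. Mailing is taken to add 5.2 points (36 − 30.8) with the container and all, half or none of that with the kit. At the clinic, the kit is taken to add 5.2 points or nothing.

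**Step 1: the plan's own figure.** The article's formula with r = 1, p1 = 0.36 and p2 = 0.31 gives (1.96·√(2·0.335·0.665) + 0.842·√(0.2304 + 0.2139))² / 0.05² = 1,398. The continuity correction, n/4·(1 + √(1 + 4/(n·0.05)))², gives 1,438. Dividing by 0.8 gives 1,798, and doubling gives 3,596. All four figures reproduce with the clinic rate rounded to 31%; the literal 30.8% would give 1,291 and 1,329. The steps below use 30.8%.

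**Step 2: power of the pooled contrast.** With n per cell, SE = √(Σp(1−p)/(4n)) and power ≈ Φ(d/SE − 1.96). Cells are ordered clinic+container, clinic+kit, mail+container, mail+kit.

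Example with nil gain from mailing with the kit, cells 30.8/36/36/36%:
- d = 36 − (30.8 + 36)/2 = 2.6 points.
- Σp(1−p) = 0.2131 + 3·0.2304 = 0.9043.
- At n = 719, SE = √(0.9043/2,876) = 0.01773, d/SE = 1.466, power 31%.
- At n = 899, SE = 0.01586, d/SE = 1.640, power 37%.

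| Mailing gain with the kit | Pooled difference | Power, kit adds 5.2 points: 1,438 (1,798) per side | Power, kit adds nothing |
|---|---|---|---|
| 5.2 points (additive) | 5.2 | 83% (90%) | 84% (91%) |
| 2.6 points | 3.9 | 59% (69%) | 61% (70%) |
| 0 | 2.6 | 31% (37%) | 32% (39%) |

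With a 5-point effect on a 31% clinic rate and no kit effect, the left-hand figures become 81%, 57% and 30%, so the rounding does not matter here.

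**Step 3: power of the test that is named.** For the 3-df chi-square, λ = n·Σ(p − m)²/(m(1 − m)), where m is the mean of the four rates. For 30.8/36/36/36%, m = 0.347, Σ(p − m)² = 0.039² + 3·0.013² = 0.002028 and m(1 − m) = 0.2266. So λ = 6.4 at 719 per cell and 8.0 at 899, and power is about 55% and 66%. A significant result here would reflect the clinic+container group falling below the other three; the test does not assign that to mailing or to the kit.

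**Step 4: what the missing estimates could deliver.**
- Interaction: SE = √(Σp(1−p)/n). In the same cells, 1.96·√(0.9043/719) = 7.0 points and 1.96·√(0.9043/899) = 6.2 points. Power for a 5.2-point interaction is 31% (37%), or 32% (39%) if the kit adds nothing.
- Mailing effect with the container: SE = √((0.2131 + 0.2304)/n), half-width 4.9 points at 719 and 4.4 at 899. Power for 5.2 points is about 55% and 65%.

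**The case against.** Sizing a factorial trial on one main effect is standard practice, and the pooled contrast remains a valid average over randomised devices even if the effects do not add. That stands. The fault is that the assumption is unstated and unchecked, not that the main effect was used for sizing.

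A reader might infer that sub-additivity would hide a real mailing benefit. The documents do not support that. The pooled contrast appears only in the sample size section. The test actually named compares four unpooled groups, all four rates would be visible, and its power in the extreme case is 55–66% rather than 31–37%. The extreme case is also only one assumption: with the gain halved, pooled power is still about 59–70%. The proper word is could.

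A reader might also infer that interaction and device-specific effects are absent from the analysis. The logistic model's terms are simply not listed. Indicators for each group against the control group would give the mailing effect with the container directly, and an article may leave model terms to a fuller document. So the point does not rest on those terms being missing. It rests on the three things the article does fix (the pooled sizing contrast, the omnibus test and the best-strategy aim), which do not fit together.

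Finally, the added estimates will be imprecise, and they will not prove a ranking of four combinations. That stands as a limit on the remedy, and it is why softening the aim is offered as an alternative.

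**Conclusion.** The point holds in a limited form. The sample size section relies on a contrast averaged over devices without saying that a single mailing effect requires additivity. The only compliance test named in the analysis section cannot deliver the aim set in the Background.

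The possible loss on the sized contrast runs from none to a fall from 83–84% to about 31% at 1,438 per side (from 90–91% to about 37% at 1,798). Which figure applies depends on an interaction the article does not quantify. All these figures assume that mailing adds 5.2 points with the container, and they use a normal approximation. Nothing in the article shows that an interaction exists. Nor does the point call for powering the trial on one: with 31% as base, a 5-point interaction would need about 2,739 analysed per cell, 10,956 in all, against the 3,596 to be enrolled.

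**What to change.** - **Sample size calculation:** state that the mail-versus-clinic contrast is an average over devices, and that reading it as one mailing effect assumes additive effects on the difference scale.
- **Statistical analysis:** estimate mail versus clinic and kit versus container from the factorial model. Report the mail-by-device interaction, the mailing effect within each device and the device effect within each route, each with a 95% confidence interval. Report them whatever the interaction p-value, and do not let that p-value choose the analysis.
- **Background aim:** base any statement about the best combination on these estimates, or soften the aim.

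The cost is wording and one model term on data already being collected, with no added participants. The price is imprecision: about ±6.2 to 7.0 points for the interaction and ±4.4 to 4.9 points for mailing with the container. Power for a 5.2-point interaction stays below 40%, so the text should say that a non-significant interaction is not evidence of no interaction.

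### The printed sample size does not follow from the printed rates: 30.8% vs 36% needs 1,291 per group, not 1,398, and the loss allowance should read 360, not 350

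*Protocol article*

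**What the plan says.** The Sample size calculation section of the protocol article compares two groups defined by how the stool device is received, mail (p1) or clinic (p2). It prints a pooled-variance formula for two proportions and gives these inputs:

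- Clinic rate: "The expected compliance rate of participants visiting a clinic is based on that observed in 2010 by the NCSP, which was 30.8" (percent).
- Mail rate: "the compliance rate of participants receiving stool devices by mail is estimated at 36" (percent), "based on the assumption that the rate will be at least 5% greater".
- Error rates: "using a two-tailed test and 80% power (1-β) at a 5% significance level".

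The Trial design section gives "allocation ratio1:1:1:1", so mail versus clinic is 1:1 and r = 1 in the formula.

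The results follow in three steps. First, "Based on the above formula, 1,398 people will be needed in each group to detect the difference". Second, a continuity correction raises this to 1,438. Third, for 20% loss to follow-up, "we will enroll an additional 350 participants per group, resulting in a final total for each group of 1,798 participants", which makes 3,596 in total.

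**The concern.** The formula, every input and every result are printed, so the calculation can be checked from the text alone. Two steps fail the check. The uncorrected and continuity-corrected sizes are both about 8% larger than the stated rates require, too much to be rounding of the result. The addition for loss to follow-up does not lead from the preceding figure to the final one.

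What is at stake is the meaning of the design statement. A reader cannot tell whether the trial was sized for a difference of 5.0 or 5.2 percentage points, and the stated 80% power does not belong to the stated rates at the stated size. A results paper that repeats the paragraph would carry the mismatch forward.

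**Working it through.** **Inputs.** p1 = 0.36, p2 = 0.308, two-sided alpha 0.05 (z = 1.960) and power 0.80 (z = 0.8416), all from the Sample size calculation section; r = 1 from the Trial design section.

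**Formulas.** With r = 1 the printed formula is

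n = {1.960 × √[2 p̄(1 − p̄)] + 0.8416 × √[p1(1 − p1) + p2(1 − p2)]}² / (p1 − p2)².

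The article does not print its continuity correction. I assume the usual form for equal groups, n_cc = (n/4) × {1 + √[1 + 4/(n(p1 − p2))]}². Loss is allowed for by n_cc / (1 − 0.20), with n_cc rounded up first.

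**1. Reproducing the printed figures.** They come out with 31% vs 36%:

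- p̄ = 0.335; the two root terms are 0.6675 and 0.6666.
- n = (1.3083 + 0.5610)² / 0.05² = 3.4941 / 0.0025 = 1,397.6, so 1,398.
- n_cc = 1,437.4, so 1,438.
- 1,438 / 0.8 = 1,797.5, so 1,798; 2 × 1,798 = 3,596.

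All four printed sizes are matched, which also supports the assumed correction and rounding.

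**2. The stated rates, 30.8% vs 36%.**

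- p̄ = 0.334; the two root terms are 0.6670 and 0.6660.
- n = (1.3073 + 0.5605)² / 0.052² = 3.4887 / 0.002704 = 1,290.2, so 1,291.
- n_cc = 1,328.4, so 1,329.
- 1,329 / 0.8 = 1,661.25, so 1,662; 2 × 1,662 = 3,324.

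**3. Exactly 5 points above 30.8%, i.e. 30.8% vs 35.8%.** n = 1,393.5, so 1,394; n_cc = 1,433.2, so 1,434. This is close to the printed pair but not equal to it.

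| Clinic vs mail | n | with continuity correction | after 20% loss | total |
|---|---|---|---|---|
| Printed in the article | 1,398 | 1,438 | 1,798 | 3,596 |
| 31% vs 36% | 1,398 | 1,438 | 1,798 | 3,596 |
| 30.8% vs 36% (as stated) | 1,291 | 1,329 | 1,662 | 3,324 |
| 30.8% vs 35.8% | 1,394 | 1,434 | 1,793 | 3,586 |

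**4. Other methods at the stated rates, alpha, sidedness and power.** Unpooled variance gives 1,288, simple pooled variance 1,292 and the arcsine method 1,290. None comes near 1,398. A one-sided test would need 1,017 at 80% power. One-sided at 90% power gives 1,408 and 1,446, near the printed pair but contrary to the stated test and power.

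**5. Size of the gap at the stated rates.** 1,398 − 1,291 = 107 per group (107 / 1,291 = 8.3%); 1,438 − 1,329 = 109; 1,798 − 1,662 = 136, or 272 in total.

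**6. Power for 30.8% vs 36% at 1,438 per group.** 83.1% on the continuity-corrected basis, on which 1,438 was derived, and 84.1% without the correction.

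**7. Loss allowance.** 1,438 + 350 = 1,788, whereas 1,798 − 1,438 = 360. The 350 matches the allowance on the uncorrected size: 1,398 / 0.8 − 1,398 = 349.5. The final 1,798 is the right inflation of 1,438.

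**The case against.** The strongest defence is that 36% is a rounded value and that the design quantity is a 5-point difference, since the text rests the mail rate on an increase of at least that much. On that reading 30.8% vs 35.8% falls within 0.3% of the printed sizes and 31% vs 36% matches them, so the fault is an unstated rounding and not a wrong derivation. This is probably how the figures arose, and it limits the weight of the point. It does not make the text right: the section states 30.8% and 36%, attributes 1,398 to the printed formula, and nowhere mentions 31% or 35.8%.

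It is also fair to say that the end of the chain is sound. 3,596 follows from 1,438 and 20% loss and agrees with the Abstract, so 350 is a wrong intermediate number that alters no enrolment figure.

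Two stronger readings are tempting, and the document supports neither. A reader might infer that a faulty calculation leaves the trial too small. The opposite holds for the stated rates, and even at 30.8% vs 35.8% the power at 1,438 is 80.1% with continuity correction. A reader might also infer from the alternative hypothesis, printed as p1 > p2, that the test or the size is one-sided. The text says two-tailed and the formula uses Z at α/2, so alpha and sample size are unambiguous and the mismatch is one of presentation.

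**Conclusion.** The point holds as a reporting error in the primary sample size calculation. The stated rates require 1,291, 1,329 and 1,662 per group where the article prints 1,398, 1,438 and 1,798, an excess of 136 per group (272 in total) at the last step. The loss allowance is misprinted by 10 per group. The error is conservative: power for the stated mail-versus-clinic contrast is about 83%, not 80%, at 1,438 analysable per group, and the planned enrolment need not change.

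This rests on 1:1 allocation between mail and clinic and on the usual form of the continuity correction. That 31% was the clinic rate used is an inference from the exact match; only the trial team can confirm it.

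**What to change.** Keep 3,596 and correct the Sample size calculation section:

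1. Make rates and size agree, in one of two ways. Either state the rates actually used, if these were 31% vs 36%, as a 5-point difference with 31% described as the rounded 2010 figure. Or keep 30.8% vs 36% and restate the power at 1,438 analysable per group as about 83% with continuity correction (84% without), saying which basis is meant.
2. Replace 350 by 360.
3. Optionally, write the alternative hypothesis as p1 ≠ p2 to match the two-tailed test. This has no numerical effect.

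The cost is the wording of one paragraph. Enrolment, design and analysis stay as they are.
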